## Abstract

**Background:**

The aim of this study is to assess if peer counseling of women improves breastfeeding, complementary feeding practices, and child growth, and thus reduces the prevalence of undernutrition in children up to 4 years of age.

**Objective:**

Lack of exclusive breastfeeding and inappropriate complementary feeding are critical factors in reducing child undernutrition, morbidity, and mortality. There are reported trials of peer counseling to improve breastfeeding; however, they did not examine the efficacy of peer counseling to improve complementary feeding or the long-term impacts on child growth and development.

**Methods:**

This study has used a community-based, cluster-randomized controlled trial with a superiority design and 2 parallel treatment arms. It is assessing the impact of peer counseling, starting in late pregnancy up to 1 year after delivery, on child feeding practices, growth, and development with follow-up until 48 months of age. The study site was Mirpur, a densely populated area in Dhaka. Using satellite maps and geographic information system mapping, we constructed 36 clusters with an average population of 5000 people. We recruited pregnant women in the third trimester aged 16-40 years, with no more than 3 living children. Trained peer counselors visited women at home twice before delivery, 4 times in the first month, monthly from 2 to 6 months, and again at 9 and 12 months. Trained research assistants collected anthropometric measurements.
The primary outcome will be differences in child stunting and mean length for age at 6, 12, 15, and 18 months. Secondary outcomes will be differences in the percentage of women exclusively breastfeeding in the mean duration of any breastfeeding and in the percentage of children at 6 and 9 months of age who receive solid, semisolid, or soft foods; and the percentage of children consuming foods from 4 or more food groups at 9, 12, 15, and 18 months. We will assess the mean cognitive function scores from the Ages and Stages Questionnaire (9 and 18 months) and Bayley tests (24 and 36 months).

**Results:**

We identified 65,535 people in mapped residences, from which we defined 36 clusters and randomly allocated them equally to intervention or control groups stratified by cluster socioeconomic status. From July 2011 to May 2013, we identified 1056 pregnant women and 993 births in the intervention group and 994 pregnancies and 890 births in the control group. At 18 months, 692 children remained in the intervention group and 551 in the control group. From January 2015 to February 2017, we conducted the long-term follow-up of the cohort. We have now completed the data collection and processing and have started analyses.

**Conclusions:**

This study will help fill the evidence gap about the short- and long-term impact of peer counseling on improving infant feeding, preventing childhood undernutrition, and enhancing child cognitive development.

**Trial Registration:**

ClinicalTrials.gov NCT01333995; https://clinicaltrials.gov/ct2/show/NCT01333995

**International Registered Report Identifier (IRRID):**

DERR1-10.2196/31475

## Introduction

Although progress has been made in reducing child undernutrition [1], it remains a highly prevalent condition in low- and middle-income countries [2]. South Asia has a major portion of the global burden of childhood undernutrition, with an estimated 59 million (or 33.3%) of children under 5 years living with stunted growth in this region [3]. Undernutrition contributes to 45% of deaths in children under 5 years old [4], and effective interventions are needed to reduce its prevalence, particularly in countries with high prevalence. In Bangladesh, child undernutrition is an important public health problem, with 36% of children younger than 5 years being stunted, 33% being underweight, and 14% being wasted in 2014 [5].

Suboptimal breastfeeding increases the risks of childhood morbidity, which potentially contributes to the development of undernutrition and mortality, particularly in the first 2 years of life [2]. The World Health Organization (WHO) recommends exclusively breastfeeding children until 6 months of age, and after that, continuing breastfeeding with appropriately diverse and frequent complementary foods [6,7]. The complementary feeding period from 6 to 24 months also provides a window of opportunity for preventing undernutrition [8] as most postnatal growth faltering occurs during the first 2 years of life. Studies have shown that even with optimum breastfeeding, growth faltering will occur if children do not receive an adequate quantity and quality of complementary foods after 6 months [9].

A study from 2016 has shown that most stunting occurs in the first 2 years [10]. This growth retardation happens because children have a higher demand for nutrients and a higher rate of infectious diseases such as diarrhea, which adversely affects growth and nutritional status [11]. A lack of diversity of foods given to young children also contributes to undernutrition. For example, animal-source foods are an important source of protein and micronutrients, such as zinc, and low intakes of these foods are associated with stunting in children [8]. Improved breastfeeding practices and more diverse foods, and increased frequency of complementary feeds can help protect infants from childhood undernutrition and improve their developmental potential.

Growth faltering, in turn, has effects on a child's developmental potential [12,13]. The South Asian region also harbors a very high proportion of children with low cognitive and socioemotional Early Childhood Development Index scores [14]. Few studies have examined the relationship between undernutrition and cognitive development in Bangladeshi children. The evidence available comes mainly from 5 trials of psychosocial stimulation [15-19]. In all these studies, malnourished children had very low developmental scores, which were significantly lower than those of better-nourished children. In micronutrient supplementation trials, children's height-for-age and weight-for-age *z* scores were significantly correlated with their developmental levels, indicating a close association of nutritional status and child development [20-25].

A systematic review and meta-analysis of 110 studies for breastfeeding promotion found statistically significant increases in exclusive breastfeeding (EBF) rates: 43% at day 1, 30% at <1 month, and 90% at 1-5 months. Rates of “no breastfeeding” reduced by 32% at 1 day, 30% at <1 month, and 18% at 1-5 months [26]. An established approach to promoting appropriate breastfeeding practices in low- and middle-income countries involves local peer counselors providing information and support to mothers feeding young children [27,28]. A systematic review showed that in low- and middle-income countries, compared to usual care, community-based peer support increased EBF in the first 6 months and initiation of breastfeeding within the first hour of life, and decreased the risk of prelacteal feeding [29]. There is research demonstrating the feasibility of implementing a peer-counseling intervention in urban Bangladesh with evidence of changed feeding behaviors [28]. To date, there have been few reports of using peer counseling to educate, support, and build a mother's skills regarding both breastfeeding and appropriate complementary feeding. A before-and-after study conducted in a lower socioeconomic population in the Lalitpur district of Uttar Pradesh, India, suggests that peer counselors can improve infant feeding practices by increasing EBF and appropriate complementary feeds [30]. However, there is a need to examine the impact of peer counseling interventions on long-term child undernutrition, growth, and development.

We used the Standard Protocol Items: Recommendations for Interventional Trials (SPIRIT) guideline [31] to prepare this protocol. It was peer reviewed by the Australian National Health and Medical Research Council (NHMRC) grant review panels in 2009 (GNT63329) and 2013 (GNT1071005) and by the Research Review Committee of the International Centre for Diarrheal Disease Research-Bangladesh (icddr,b). The University of Sydney Human Ethics committee and the Ethics Review Committee of ICDDR-B approved the protocols. This report combines the 2 approved protocols.

We aim to implement a community-based, cluster -randomized controlled trial to collect evidence of whether peer counseling of women to promote appropriate infant feeding can improve breastfeeding, complementary feeding, and child growth, and thus reduce the prevalence of stunting (low height-for-age) in their children up to 18 months of age. In addition, the proposed study will examine the long-term impact of peer counseling for appropriate infant feeding on child anthropometry and cognitive development at 36 and 48 months.

Our primary hypothesis is that in a community-based, cluster-randomized controlled trial of peer counseling to support infant feeding starting from the third trimester of pregnancy to 1 year after delivery will reduce the prevalence of stunting (length-for-age < –2 z score) in children at 18 months of age by 10% compared to the control group with no peer counseling.

The short-term outcomes (secondary hypotheses) are the following:

1. The percentage of children with low length-for-age, low weight-for-height, and low weight-for-age between 6 and 18 months of age will be lower in the peer counseling group than in the control group.

2. The mean length-for-age, weight-for-height, and weight-for-age in children between 6 and 18 months of age will be higher in the peer counseling group than in the control group.

3. The children's height and weight velocity from birth to 18 months of age will be higher in the peer counseling group than in the control group.

4. The percentage of women EBF (breast milk and no other foods or milk-based liquids) their infants at 3 and 6 months will be higher in the peer counseling group than in the control group.

5. The mean duration of any breastfeeding will be longer in the peer counseling group than in the control group.

6. The percentage of women bottle feeding (any liquid or semisolid food from a bottle with a nipple or teat) their infants at 12 months will be lower in the peer counseling group than in the control group.

7.The percentage of children at 6 and 9 months of age who receive solid, semisolid, or soft foods will be higher in the peer counseling group than in the control group.

8. The percentage of children consuming >4 food groups at 9, 12, 15, and 18 months will be higher in the peer counseling group than in the control group.

9. Mean intake of children’s food energy, protein, carbohydrate, fat, and selected micronutrients (eg, zinc, iron, phytate vitamin A) from complementary feeds at 9, 12, 15, and 18 months will increase more in the peer counseling group than in the control group.

10. The mean days ill with diarrhea, acute respiratory illness, and fever at each monthly recall period from 1 to 18 months will be lower in the peer counseling group than in the control group.

The longer-term outcomes (secondary hypotheses) are the following:

1. The percentage of children with low length-for-age, low weight-for-length, and low weight-for-age in children between 18 and 48 months of age will be lower in the peer counseling group than in the control group.

2. The mean length-for-age, weight-for-length, and weight-for-age of children between 18 and 48 months of age will be higher in the peer counseling group than in the control group.

3. The children's length and weight velocity from 18 to 48 months of age will be higher in the peer counseling group than in the control group.

4. Mean cognitive, language, and motor composite scores as measured by the Ages and Stages Questionnaire and Bayley Scales of Infant and Toddler Development at 48 months of age will be higher in the peer counseling group than in the control group.

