### Secondary Outcomes to be Measured

We measured changes in the percentage of women EBF (breast milk and no other foods or milk-based liquids) their infants from 1 to 6 months. We also measured changes in the mean duration of any breastfeeding. We calculated the changes in the percentage of children at 6 and 9 months of age who received solid, semisolid, or soft foods; and the percentage of children consuming foods from 4 or more food groups at 9, 12, 15, and 18 months. We assessed bottle feeding (any liquid or semisolid food from a bottle with a nipple or teat) in infants at 7, 9, and 12 months. We measured the changes in mean cognitive function scores with the Ages and Stages Questionnaire (9 and 18 months) and Bayley tests (24 and 36 months).

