#### Infant Feeding Practices

We collected infant feeding data every month from birth to 6 months, and then at 3-month intervals between 6 and 18 months. We applied the standard Bangladesh Demographic Health Survey (DHS) questions about infant-feeding practices [37] and monitored these patterns at the 3 monthly data collection periods from birth until 18 months of age. These include questions about current breastfeeding status, current use of other liquids and solid foods, the timing of introduction of other liquids or solid foods, use of bottles for feeding, and information about who was providing advice about infant feeding among family and friends.

A senior research assistant monitored about 10% of the interviewer's scheduled visits. The supervisors checked questionnaires daily, and if the information was incomplete or not clear, they returned to the home on the next day to complete the data form. Senior research assistants verified the mother's reports of infant feeding practices through a 4-hour observation period in an unscheduled visit.

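### Exclusive breastfeeding as worded admits water and other non-milk liquids, the food-diversity cut-off is stated two ways, and two feeding hypotheses compete at 6 months

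*Protocol article*

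**What the plan says.** **Exclusive breastfeeding.** Introduction, short-term hypothesis 4, predicts a higher value with counselling for "The percentage of women EBF (breast milk and no other foods or milk-based liquids) their infants at 3 and 6 months". Methods, Secondary Outcomes to be Measured, keeps the parenthesis but changes the ages: "EBF (breast milk and no other foods or milk-based liquids) their infants from 1 to 6 months". Methods, Infant Feeding Practices, says that the questionnaire covers "current use of other liquids and solid foods".

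**Solids.** Hypothesis 7 reads: "The percentage of children at 6 and 9 months of age who receive solid, semisolid, or soft foods will be higher". Methods uses the same two ages: "the percentage of children at 6 and 9 months of age who received solid, semisolid, or soft foods". The Introduction places the change of feeding mode at the same age, since the WHO "recommends exclusively breastfeeding children until 6 months of age, and after that, continuing breastfeeding with appropriately diverse and frequent complementary foods".

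**Food diversity.** Hypothesis 8 reads: "The percentage of children consuming >4 food groups at 9, 12, 15, and 18 months will be higher". Methods has "the percentage of children consuming foods from 4 or more food groups at 9, 12, 15, and 18 months", and the Abstract agrees with Methods.

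**The concern.** These outcomes test the path through which counselling is meant to improve growth, so a coding rule that puts children in the wrong class matters even though the outcomes are secondary.

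- The breastfeeding parenthesis names two exclusions, foods and milk-based liquids. Water and other non-milk liquids are in neither. If foods were meant to cover every liquid, there would be no need to name milk-based ones.
- More than 4 means 5 or more. The two cut-offs define different successes for the same outcome at the same four ages. The Results section says that data processing is finished and analyses have begun, so an unresolved cut-off leaves a choice open when results can be seen.
- An infant who takes no other food cannot also be receiving solids. At 6 months the plan predicts a rise in both percentages and does not say how to read them together.

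**Working it through.** The plan gives no figure on this point to reproduce. The check sets the definitions side by side and works out what follows from each. Every share below is an assumption, because the documents report none.

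**1. Exclusive breastfeeding.** In each arm let E be the share on breast milk and nothing else, and W the share on breast milk plus non-milk liquids only. The wording scores E + W. With subscript 1 for counselling and 0 for control:

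scored difference = (E1 + W1) − (E0 + W0) = (E1 − E0) + (W1 − W0).

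The error is W1 − W0. Assume E1 = 60% and E0 = 40%, a true gain of 20 points:

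| W1 | W0 | Scored difference | Error |
|---|---|---|---|
| 10% | 10% | 70 − 50 = 20 points | 0 |
| 5% | 20% | 65 − 60 = 5 points | −15 |
| 20% | 5% | 80 − 45 = 35 points | +15 |

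The error can have either sign. The second row fits a programme that gets families to stop giving water. The third fits one that moves infants from milk feeds to breast milk plus water.

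**2. Food diversity.** The two cut-offs differ by the children who eat exactly 4 groups. To illustrate, assume 7 groups, each eaten independently with probability p:

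| p | 4 or more | More than 4 | Exactly 4 |
|---|---|---|---|
| 0.4 | 29.0% | 9.6% | 19.4 points |
| 0.5 | 50.0% | 22.7% | 27.3 points |
| 0.6 | 71.0% | 42.0% | 29.0 points |

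The difference between arms moves less than the level. With control at p = 0.4 and counselling at 0.5, it is 50.0 − 29.0 = 21.0 points under 4 or more and 22.7 − 9.6 = 13.1 under more than 4. At 0.5 against 0.6 it is 71.0 − 50.0 = 21.0 and 42.0 − 22.7 = 19.3.

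**3. The 6-month visit.** Let E be exclusively breastfed, S receiving solids and O neither. The states do not overlap, so E + S + O = 100% in each arm. Subtracting the arms gives

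(E1 − E0) + (S1 − S0) = O0 − O1 ≤ O0.

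Both hypotheses can hold at 6 months only if O is smaller under counselling, and the two gains together cannot exceed the control arm's O. Assumed values for O0 of 0, 5, 10, 20 and 30% cap the combined gain at 0, 5, 10, 20 and 30 points. Under the strict definition, infants on breast milk plus water fall into O, so the definition in item 1 also sets this ceiling.

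**The case against.** The case for leaving the text alone has force in several places.

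- **The label says exclusive, and a short parenthesis in an article need not be the coding rule.** No passage says that infants given water will be coded as exclusively breastfed, and other liquids are asked about. This supports a stricter intent. But the same parenthesis is given twice, nothing else in the article corrects it, and an analyst following it would code it as written.
- **The more-than-4 wording may be a typographical slip.** That is plausible, since the Abstract and Methods agree with each other. The documents cannot confirm it, and the correction is needed either way.
- **A reader might infer that hypotheses 4 and 7 contradict each other, so that the 6-month result has no readable direction.** The documents do not support this. The hypotheses concern percentages, and infants in neither state can move into either one. The section on visits from 2 to 6 months says that complementary-feeding messages begin at 5 months, so counselling could raise receipt of solids at 6 months as well as delay it. Exclusive breastfeeding is also assessed at earlier ages.
- **A reader might infer that admitting water must dilute the effect.** That holds only if counselling lowers the share given non-milk liquids. Equal shares give no error, and a higher share under counselling inflates the effect.
- **Moving exclusive breastfeeding to an earlier age and testing solids at 9 months only would remove the overlap.** It would also change stated time points after data collection, which is the kind of post-data choice that the point about the cut-off warns against.

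**Conclusion.** The point holds for two secondary outcomes. The exclusive breastfeeding definition, followed literally, misclassifies infants given water or other non-milk liquids. The resulting error in the group difference equals the between-arm difference in that share, and its size and sign cannot be determined from the documents. The diversity cut-off is a plain contradiction. It moves the reported percentage by the share of children eating exactly 4 groups, 19 to 29 points under the independence assumption used here. The 6-month overlap is a real but partial competition, bounded by the control arm's share in neither state, which is not given.

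A reader might take this as a threat to the trial's main result. It is not: the 18-month stunting comparison and the sample size use none of these definitions.

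**What to change.** 1. Define exclusive breastfeeding as breast milk with no other food or liquid, including water, in both the hypotheses and Methods. Code it from the other-liquids items already collected, assuming that water is among the liquids asked about, since the article does not list them.
2. Reconcile its ages, which are 3 and 6 months in hypothesis 4 and 1 to 6 months in Methods. Infant Feeding Practices describes both monthly and 3-monthly collection. Months 3 and 6 are covered on either reading; for the other months, confirm that the liquids items were asked.
3. Use 4 or more food groups throughout, as the Abstract and Methods already do, and record this before the outcome is analysed by arm.
4. Keep the planned 6-month time point. Report it as one classification (exclusively breastfed, receiving solids, neither) by arm, and read hypotheses 4 and 7 together from that table.

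The cost is recoding, rewording and one extra table, with no new data. The downside is that the strict definition can only lower the exclusive breastfeeding percentages in both arms, or leave them unchanged if no infant received non-milk liquids alone.

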## Methods

### Study Design

The study is a community-based, cluster-randomized controlled trial with a superiority design and 2 parallel treatment arms with a 1:1 allocation ratio. It examines the impact of a peer-counseling infant-feeding education program starting in the third trimester of pregnancy to 1 year after delivery on child feeding practices, growth, and development (Figure 1). We followed the cohort of the mother-child dyads from recruitment until the children were 48 months of age.

**Figure 1 figure1:**
[figure not shown]
The Shishu Pushti study design. MCH: mother and child health; SES: socioeconomic status.

### Study Setting

We conducted the trial in Mirpur, an area of approximately 39 square kilometers located in the northwest of Dhaka City, Bangladesh. It has 16 wards (administrative regions), of which 4 wards were selected for the trial where there were no other major health or nutrition studies ongoing. Mirpur is a middle-to-lower socioeconomic area in Dhaka, but it includes very disadvantaged slum areas.

### Identification of Clusters

The study site is a very densely populated and includes areas of slum housing where there are no established addresses and houses are very close to each other against each other along narrow paths. In this setting, there were no administrative or natural boundaries to define clusters. For the trial, we used satellite maps of the study areas in Mirpur to define clusters with buffer areas. We digitalized all structures, buildings, roads, and water bodies from satellite maps of the study area and gave each structure an identification number. Our field census team visited all the structures and buildings in the study area and identified if it was a residence or was used for other purposes. After obtaining written informed consent, we conducted a brief household census and screened for pregnant women in all residential buildings. We used the census data to create a population database linked to the mapped structures. Using geographic information system mapping techniques, we constructed 36 clusters from the population maps to cover an average population of 5000 people with a surrounding 200-meter buffer zone between clusters. We classified each cluster as low socioeconomic status or not based on the census data. Figure 2 shows a map of the study site.

